### 2.5. Outcomes Measurement

The two primary outcomes will be assessed using the two assessment tools used in the 2010 American College of Rheumatology (ACR) FM diagnostic criteria, validated for use in the Spanish population, with a cut-off score of WPI ≥ 7 and SS ≥ 5 or WPI 3–6 and SS ≥ 9 [22]. [name] and [name] will be in charge of the post-treatment evaluation of the subjects, as well as the evaluation at each of the follow-ups, although all the questionnaires included are self-completed. Both members of the research team are clinicians with 10 years of daily experience, as well as professors of manual therapy at the European University of Madrid (Spain).

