### 2.2. Sample

Fifty-two consecutive patients younger than 65 years who meet the American College of Rheumatology (ACR) clinical criteria for FM [20] will be included in the study. Patients will be recruited by the center’s staff, who will be blinded to the severity of Fibromyalgia assessment performed. The center’s staff will be in charge of promoting the study through their direct contact, both in group activities and through individual talks. Individuals who will be included in the study will have a minimum one-year history of symptoms. To this medical diagnosis will be added a clinical evaluation based on the 2010 American College of Rheumatology (ACR) criteria [21], performed by the physical therapists and investigators participating in the study ([name] and [name]): given that 2 of the measurement variables that will be used in the study (widespread pain index, WPI; and symptom severity index, SS-Score) coincide with the protocol, when determining these criteria, the diagnosis of fibromyalgia will be corroborated when WPI ≥ 7 and SS ≥ 5 or WPI 3–6 and SS ≥ 9 [22]. The exclusion criteria will be: the receipt of any non-pharmacological therapy, presence of cardiac, renal or hepatic failure, severe physical disability, comorbidities (e.g., interstitial cystitis, inflammatory disease), infection, fever, hypotension, respiratory disorders limiting treatment, herpes, lupus, multiple sclerosis, rheumatoid arthritis, polio, epilepsy, rheumatic fever, cancer, history of neck or back surgery, skin disorders, psychiatric disease, non-compliance with the prescribed drug therapy, and pregnant women or with the possibility that they could be pregnant due to the incompatibility of the techniques [14,15,16,17,23].

In addition, out of twenty-three patients, thirteen finally met all the requirements and criteria and were recruited to present preliminary results by conducting a pilot study in order to provide a clearer description of the protocol.

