#### Sample Size

The latest version of the free GRANMO program version 7.12 was used. The sample size of 52 randomly distributed patients will provide at least 80% statistical power to detect a difference of 14 units between the two groups in the FIQ inventory. This calculation assumes a bilateral significance level of 5% and a standard deviation of 17. In addition, a loss rate of 10% was calculated until the end of the study.

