#### 2.5.1. Widespread Pain

This will be classified as a continuous numerical variable measured by the widespread pain index (WPI). In this index, the patient has to mark with an x the areas in which he/she has presented pain during the last week. The WPI is a valid pain extension scale that was previously described as a regional pain scale and is comprised of a list of 19 painful body areas, where patients indicate whether a specific painful area is painful on a scale ranging from 0 to 19 [28].

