#### 2.5.2. Symptom Severity

This variable will be classified as a continuous numerical variable, measured by the symptom severity index (SSI/SS-Score), composed of two subscales (SS-1 and SS-2) that assess the intensity during the last week of 3 of the main symptoms present in FM (fatigue, unrefreshing sleep and cognitive disorders), as well as the presence/absence of other common symptoms, respectively. The total score of the SSS is the sum total and ranges from 0 to 12. The SSS correlated correlates strongly with the WPI (r = 0.733) and with the presence of tender points (r = 0.680) [29].

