#### 2.5.3. Impact of FM on Quality of Life

Another measurement variable will be the impact of fibromyalgia on quality of life, through the fibromyalgia impact questionnaire (FIQ), a tool translated into Spanish by means of international translation–retrotranslation recommendations [21], and whose reliability, validity, adaptation and sensitivity to change has been satisfactorily analyzed in Spanish patients with FM [30,31]. This questionnaire consists of 19 items that measure three main categories (a) “function”—ten items that assess the participant’s physical functions that address the participant’s ability to perform each activity. This domain will be assessed on a 4-point Likert scale, from 0 to 3 (0 = always, 1 = frequently, 2 = occasionally, 3 = never). (b) “Global impact”—composed of two items assessing the number of days in the last week when the participants felt good and the number of days they could not work due to FM symptoms.

In addition, the EuroQol 5-dimensions 5-levels (EQ-5D-5L) will be used: a test where mobility, self-care, activities of daily living, pain/discomfort and anxiety/depression are assessed [32]. The patient himself assesses his state of health, in levels of severity by dimensions. The first allows the respondent to define the state of health according to the EQ-5D multi-attribute classification system, composed of 5 dimensions (mobility, self-care, activities of daily living, pain/discomfort and anxiety/depression), and in each of them there are 3 levels of severity (1, 2 or 3).

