### 2.6. Statistical Analysis

The distribution of quantitative variables will be analyzed with the Kolmogorov– Smirnov test, to evaluate the normality of the samples to verify if there are significant differences in the two samples at baseline, as well as at different times (*p* > 0.05). The t-test will be used for comparison of characteristics between the different groups at baseline. The chi-square test will be used to assess the independence of the categorical baseline data. The mean, SD and 95% CI will be calculated for all variables. Repeated-measures analyses of variance (ANOVA) with two factors (2 (treatment groups) × 5 (time: baseline, immediately after intervention, and at one month, two months and three months after the study started)) will be performed for the FIQ and NPRS scores. The comparisons for time factor for all variables and for each group will be applied to the group. Time comparisons for all variables and for each group the proportion of subjects who have an improvement than the NPRS MCID (2.0 points) or the FIQ MCID (14%) will be calculated and will be compared between groups using the *p* value [26,49]. The effect size will be calculated for the NPRS and FIQ variables. *p* values associated with F statistics will be adjusted for ANOVA via the Greenhouse–Geisser correction. Statistical significance will be set at *p* value of <0.05 for all calculations. 

For the analysis of the pilot study, the data were analyzed with the SPSS package version 25.0 (SPSS Inc, Chicago, IL, USA). The homogeneity of the sample in both groups was examined at the beginning of the study with respect to the variables studied to detect statistically significant differences using the Mann–Whitney U test. Descriptive statistics, including frequency counts for categorical variables and measures of central tendency and dispersion for continuous variables, were calculated to summarize the data. Paired-samples T-test was used to compare pre, post, and 1–2-month measurements of all variables studied. The Wilcoxon rank test for related samples was used to establish differences between scores before and immediately after the 4 treatment sessions, 1 month after the intervention and 2 months after the intervention in the two groups. For all study data, *p* values less than 0.05 were considered significant.

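### The declared primary outcomes (WPI and SS) match neither the endpoint the trial is sized on (FIQ) nor the endpoints given a between-group analysis (FIQ and NPRS)

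*Protocol article*

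**What the plan says.** - **Primary outcomes.** Section 2.5 states: "The two primary outcomes will be assessed using the two assessment tools used in the 2010 American College of Rheumatology" fibromyalgia criteria. Section 2.2 identifies the tools as "2 of the measurement variables that will be used in the study (widespread pain index, WPI; and symptom severity index, SS-Score". Sections 2.5.1 and 2.5.2 treat both as continuous scores: WPI from 0 to 19, and for SS "The total score of the SSS is the sum total and ranges from 0 to 12".
- **Sample size.** The Sample Size subsection of 2.2 gives 52 patients at least 80% power "to detect a difference of 14 units between the two groups in the FIQ inventory", with two-sided 5% significance, an SD of 17 and 10% loss. It mentions neither WPI nor SS.
- **Status of FIQ.** Section 2.5.3 introduces it as follows: "Another measurement variable will be the impact of fibromyalgia on quality of life, through the fibromyalgia impact questionnaire (FIQ". It is not called primary.
- **Analysis.** In Section 2.6 the 2 (group) × 5 (time) repeated-measures ANOVA "will be performed for the FIQ and NPRS scores". The comparison of responder proportions between groups uses the NPRS and FIQ thresholds, and effect sizes are planned for NPRS and FIQ. All variables get a mean, SD and 95% CI, and comparisons over time within each group. The t-test between groups is for baseline characteristics.

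**The concern.** The aim in the Introduction is comparative: which of two manual therapy approaches is more effective. A primary outcome should therefore be the one on which the groups are formally compared and, normally, the one that justifies the number of patients. Here the designation, the sizing and the between-group analysis do not point to the same variable.

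A team that followed the text exactly would finish with no stated between-group test of either primary outcome. Within-group change over time cannot fill that gap, because improvement in one arm and none in the other is not evidence of a difference between arms. The mismatch also leaves room for choice after the data are seen. A null result on WPI and SS could be set aside in favour of FIQ because FIQ was powered, or a null FIQ result set aside because WPI and SS were primary. The article would support either account.

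**Working it through.** **1. Reproduce the stated sample size.** Inputs from the Sample Size subsection: difference 14, SD 17, two-sided 5%, 80% power, 10% loss. Equal allocation is assumed, because no ratio is stated.

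- n per arm = 2 × [SD × (1.960 + 0.842) / difference]² = 2 × [17 × 2.802 / 14]² = 23.15
- Allowing for loss: 23.15 / 0.9 = 25.72, rounded up to 26 per arm, so 52 in total.

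The stated 52 is reproduced. (Rounding to 24 before inflating would give 27 per arm, or 54, a trivial difference.) Power for FIQ is 84.4% with 26 per arm (82.9% by t-test). With 23 per arm, about what remains after 10% loss (52 × 0.9 / 2 = 23.4), it is 79.8% (78.0% by t-test). The sizing is correct for FIQ.

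**2. Set the sections side by side.**

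| Outcome | Declared primary (2.5) | Power statement (2.2) | Post-baseline between-group analysis (2.6) |
|---|---|---|---|
| WPI | Yes | None | None stated |
| SS | Yes | None | None stated |
| FIQ | No | 14 units, SD 17 | 2 × 5 ANOVA, responders, effect size |
| NPRS | No | None | 2 × 5 ANOVA, responders, effect size |

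No row is filled in all three columns. The opening sentence of Section 2.6 does mention differences between the two samples at different times, but it describes a Kolmogorov–Smirnov normality check and not a treatment comparison.

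**3. What 52 patients offer for WPI and SS.** The article gives no target difference or SD for either score, so only a standardised figure can be computed. With 23 completers per arm and 80% power:

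- Two-sided 0.05: (1.960 + 0.842) × √(2/23) = 0.83 SD (0.84 by t-test).
- Two-sided 0.025, if alpha is split equally over two primaries: 0.91 SD (0.94 by t-test).

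To put this on the scales, SDs must be assumed; none is in the article. A WPI SD of 3 to 5 would mean a detectable difference of 2.5 to 4.1 areas, and an SS SD of 1.5 to 2.5 would mean 1.2 to 2.1 points, both at 0.05. If the true effect were 0.3, 0.5 or 0.7 SD (again assumed), power per outcome at 0.05 would be about 17%, 40% or 66%.

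**The case against.** The best defence is that FIQ forms a coherent comparison. It has a difference, an SD, an alpha level and a power, then a group-by-time model with Greenhouse–Geisser correction, a responder comparison and an effect size. That stands. A reader might infer from the mismatch that the trial has no coherent confirmatory test, but the document does not support so strong a reading. The fault is that the powered and modelled endpoint is not the one designated primary.

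Three further inferences should also be resisted.

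- **An inflated error rate.** Section 2.6 sets significance at a p "value of <0.05 for all calculations", and there are two primaries and four post-baseline assessments, so a reader might attach a family-wise error rate to WPI and SS. The plan states no between-group tests of those scores, so it has no such rate to compute. Any figure would also need correlations over time that the article does not give.
- **A false power claim.** The Sample Size subsection does not claim 80% power for the primary outcome. It claims it for FIQ and never calls FIQ primary.
- **Missing detail.** A condensed article may leave the primary assessment time and the multiplicity rule to a fuller document. Nor does the absence of WPI and SS from the pilot tables count against the sizing, since the pilot is offered to illustrate the protocol. The point relies on none of these.

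A separate analysis plan does not remove the core of the point. The three sections conflict as written, and another document could resolve that only by overriding one of them.

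One caution applies to the remedy. FIQ was among the outcomes with a significant pilot change in the MTA arm (p = 0.036 after treatment and at one month), so making it primary now could look like selection on a favourable result.

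**Conclusion.** The point holds as an inconsistency between Sections 2.5, 2.2 and 2.6. The two declared primary outcomes have no power statement and no stated post-baseline between-group test, while FIQ has both without primary status. This should be corrected, because it decides which result the trial's conclusion rests on.

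The total of 52 is right for FIQ under the stated assumptions and equal allocation. Power for WPI and SS is not established. The detectable difference of 0.83 to 0.84 SD assumes about 23 completers per arm, and nothing in the article says whether an effect of that size is realistic for either score. The conclusion itself does not depend on that figure or on the assumed SDs.

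**What to change.** Settle one of the following before outcome data are seen.

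1. **Make FIQ primary.** Name the FIQ total score at one stated assessment as the single primary outcome. Move WPI and SS to secondary and analyse them with the same between-group model. State that the choice follows the basis of the sample size and not the pilot's significant FIQ change. The 52 patients stand as long as the 14-unit target does. The text should also say how that target relates to the 14% FIQ threshold in Section 2.6, which at the pilot baseline means is 0.14 × 52.28 = 7.3 and 0.14 × 54.87 = 7.7 points.
2. **Keep WPI and SS primary.** Add both to the group-by-time model, with an alpha rule such as Holm if success on either would count. State that the 80% power applies to FIQ only and that power for WPI and SS is not established, unless a justified difference and SD are supplied for each.

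The first option is a change of wording with no added patients or visits; its cost is that WPI and SS lose primary status. The cost of the second is that the power statement no longer covers the primary outcomes, and the detectable difference grows to about 0.91 SD (0.94 by t-test) if alpha is split equally. Any other public description of the outcomes should be brought into line with the choice.

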#### 2.5.1. Widespread Pain

This will be classified as a continuous numerical variable measured by the widespread pain index (WPI). In this index, the patient has to mark with an x the areas in which he/she has presented pain during the last week. The WPI is a valid pain extension scale that was previously described as a regional pain scale and is comprised of a list of 19 painful body areas, where patients indicate whether a specific painful area is painful on a scale ranging from 0 to 19 [28].

#### 2.5.2. Symptom Severity

This variable will be classified as a continuous numerical variable, measured by the symptom severity index (SSI/SS-Score), composed of two subscales (SS-1 and SS-2) that assess the intensity during the last week of 3 of the main symptoms present in FM (fatigue, unrefreshing sleep and cognitive disorders), as well as the presence/absence of other common symptoms, respectively. The total score of the SSS is the sum total and ranges from 0 to 12. The SSS correlated correlates strongly with the WPI (r = 0.733) and with the presence of tender points (r = 0.680) [29].

#### 2.5.3. Impact of FM on Quality of Life

Another measurement variable will be the impact of fibromyalgia on quality of life, through the fibromyalgia impact questionnaire (FIQ), a tool translated into Spanish by means of international translation–retrotranslation recommendations [21], and whose reliability, validity, adaptation and sensitivity to change has been satisfactorily analyzed in Spanish patients with FM [30,31]. This questionnaire consists of 19 items that measure three main categories (a) “function”—ten items that assess the participant’s physical functions that address the participant’s ability to perform each activity. This domain will be assessed on a 4-point Likert scale, from 0 to 3 (0 = always, 1 = frequently, 2 = occasionally, 3 = never). (b) “Global impact”—composed of two items assessing the number of days in the last week when the participants felt good and the number of days they could not work due to FM symptoms.

In addition, the EuroQol 5-dimensions 5-levels (EQ-5D-5L) will be used: a test where mobility, self-care, activities of daily living, pain/discomfort and anxiety/depression are assessed [32]. The patient himself assesses his state of health, in levels of severity by dimensions. The first allows the respondent to define the state of health according to the EQ-5D multi-attribute classification system, composed of 5 dimensions (mobility, self-care, activities of daily living, pain/discomfort and anxiety/depression), and in each of them there are 3 levels of severity (1, 2 or 3).

#### 2.5.4. Assessment of Perceived Pain and Sensitization-Associated

Perceived pain will be measured with the numerical pain rating scale (NPRS), which measures pain intensity [33]. The worst pain intensity at rest were assessed on a 10-point (NPRS, 0: no pain, 10: maximum pain).

The presence of self-reported, sensitization-associated and neuropathic pain symptoms will be assessed with the central sensitization inventory (CSI), which is a 25-item self-report questionnaire [34]. Each item will be evaluated on a 5-point Likert scale for a total of 0 to 100 points. A cut-off value of 40 points suggests an alteration of nociceptive pain processing.

#### 2.5.5. Sleep Quality

Sleep quality will be measured with the Pittsburgh sleep quality index (PSQI) consists of 19 self-administered questions and 5 questions assessed by the patient’s partner or roommate (if available). Only the self-administered questions are included in the score. The PSQI, developed by the Department of Psychiatry at the University of Pittsburgh in 1988, is a questionnaire that assesses both qualitative and quantitative aspects of sleep quality in the month prior to its administration. It shows that subjective sleep quality, duration, efficiency, disturbances and daytime dysfunction have better quality in those with moderate and severe impairment; while in those with average and higher performance, higher sleep latencies are observed [35]. The total score is 21, and scores above 5 indicate significant sleep disturbance.

#### 2.5.6. Physical Activity

The international physical activity questionnaire (IPAQ) will be used to assess physical activity levels [36]. The questionnaire consists of a total of seven questions, related to activities performed in the last seven days prior to the application of the questionnaire. The questions measure the principles of physical activity, such as walking, moderate and vigorous intensity activities, frequency and duration. The data obtained will be converted into MET min/week (i.e., metabolic equivalent task) by calculating the minutes scored per week in each activity category by specific metabolic equivalent in accordance with previous research [37].

#### 2.5.7. Psychological, Cognitive, and Emotional Factors

Finally, psychological, cognitive, and emotional factors will be measured, such as kinesiophobia [38,39], anxiety [40], depression [41], psychological distress [42], and self-efficacy [43,44,45]. For this purpose, we will use the Tampa scale of kinesiophobia (TSK), the state-trait anxiety inventory (STAI), the Beck depression inventory II (BDI-II), and the chronic pain self-efficacy questionnaire (PSEQ), all of them translated and validated in Spanish [45,46]. The TSK is a 17-item self-report measure that will be used to measure fear of movement. A high score indicates an extreme fear of movement, while a low score indicates a negligible fear of movement. The STAI questionnaire is used to assess two independent concepts of anxiety: trait anxiety and state anxiety, each with 20 items: anxiety as a trait indicates a relatively stable anxious propensity that characterizes individuals with a tendency to perceive situations as threatening and it is the one used when studying changes over time and the one used in this study. BDI-II is a useful tool to assess symptoms of depression, both in anxiety disorders and depressive conditions. The questionnaire consists of 21 questions, providing a range of scores between 0 and 63. The questionnaire proposes the following cut-off scores and corresponding degrees of depression: 0–13 indicates minimal depression, 14–19 mild depression, 20–28 moderate depression and 29–63 severe depression. Psychological distress will be measured with the general health questionaire-12 (GHQ-12), which consists of 12 items that survey the individual’s mental health over weeks. It offers four response options and provides scores ranging from 0 to 36, where higher scores are more indicative of mental health problems. The PSEQ is a 10-item questionnaire developed to assess the confidence that people with persistent pain have in performing activities while in pain. The PSEQ is applicable to all presentations of persistent pain. It enquires about the level of self-efficacy in relation to a range of functions, such as housework, socializing and work, as well as coping with pain without medication. 

#### 2.5.8. Patient Satisfaction

To assess patient satisfaction, the global assessment of change (GRoC) will be used [47]. The GRoC is a 15-point scale with a central value of 0 (no change) and values above or to the left ranging from −1 to −7 (much worse), and below or to the right from +1 to +7 (much better). For the study we will consider those patients who score “considerably better” or better (+5 or more) will be those who received successful treatment. It has previously been published that a score of +4 (moderately better) is a suggested cut-off point for dichotomizing improvement versus non-improvement [48].

